###### Alcohol-Related Harms

This outcome will be assessed using the 23-item Rutgers Alcohol Problem Index, which measures the consequences of alcohol use. Students would be asked to report the consequences of their alcohol use over the past 12 months, in which higher scores indicate greater harms [40].

###### Parental Self-Efficacy

Data regarding parental self-efficacy will be collected by a 3-item scale measuring parents’ confidence in their ability to prevent their adolescent from drinking alcohol, in which higher scores indicate a greater sense of self-efficacy [41]; this has been used and validated in the past PAS studies [42,43].

###### Parental Supply of Alcohol

This will be measured by a 2-question scale from the Australian Parental Supply of Alcohol Longitudinal Study (APSALS) [44] to examine the frequency and quantity of alcohol supplied by parents; higher scores indicate a higher frequency and quantity of alcohol supplied.

**Figure 6 figure6:**
[figure not shown]
Theory of Change Logic Model for *Climate Schools Plus*.

**Table 1 table1:** The timeline of student and parent or guardian participation in the study.

Timeline		*Climate Schools Plus*		Control	
		Parent	Student	Parent	Student
**Term 1, 2018**					
	Assessment	Parent survey 1: baseline	Student survey 1: baseline	Parent survey 1: baseline	Student survey 1: baseline
	Intervention	Parent modules: alcohol	Year 8 student lessons: alcohol	—	—
	Evaluation	Evaluation of alcohol modules	Evaluation of alcohol lessons	—	—
**Term 1, 2019**					
	Assessment	Parent survey 2 (12-month follow-up)	Student survey 2 (12-month follow-up)	Parent survey 2 (12-month follow-up)	Student survey 2 (12-month follow-up)
	Intervention	Parent modules: alcohol and cannabis	Year 9 student lessons: alcohol and cannabis	—	—
	Evaluation	Evaluation of alcohol and cannabis modules	Evaluation of alcohol and cannabis lessons	—	—
**Term 1, 2020**					
	Assessment	Parent survey 3 (24-month follow-up)	Student survey 3 (24-month follow-up)	Parent survey 3 (24-month follow-up)	Student survey 3 (24-month follow-up)

###### Use of Cannabis and Other Drugs

Cannabis and other drug use (tobacco or cigarettes, amphetamines, ecstasy, hallucinogens, sedatives, inhalants, or “other”) will be measured by 5 questions adapted from the National Drug Strategy Household Survey [4] and the Australian Secondary Students Alcohol and Drug Survey (2014) [38], which have been used in previous *Climate Schools* trials to measure cannabis and other drug use [18-21,23,24,37]. For example, students would be asked *“Have you used cannabis in the past 12 months?,”* in which response options are “Yes” versus “No,” and *“How often have you used cannabis in the past 12 months?,”* in which response options range from “Never” to “More than once a day,” and higher scores indicate more frequent cannabis use. This allows for comparisons between this sample and a large-scale representative group of Australians.

###### Parent-Adolescent Communication

This outcome will be measured by a 6-question scale from the APSALS, examining parental knowledge and child disclosure of activities, friends, and whereabouts (eg, *“I usually know what my child is doing after school*,*”* with response options ranging from “Never” to “Always”; higher scores indicate a higher quality of communication). This outcome will also be measured by the 20-item Parent-Adolescent Communication Scale [45], which measures how cohesive and adaptable communication is between parents and children (eg, *“I can discuss my beliefs with my child without feeling restrained or embarrassed”* with response options ranging from “Strongly Disagree” to “Strongly Agree”).

###### Alcohol-Related Knowledge

Alcohol-related knowledge will be assessed using a 16-item “Knowledge of Alcohol” scale originally adapted from the School Health and Alcohol Harm Reduction Project (SHAHRP) questionnaire and used in previous trials of the *Climate Schools* programs [18-21,23,24,37,46]. Students and parents would be required to answer “True” or “False” to each item (eg, *“The recommended guidelines say that it is OK for adults to have up to 2 drinks on any one day”*), and a greater proportion of correct answers indicates greater alcohol knowledge.

###### Cannabis-Related Knowledge

Parents’ and students’ knowledge about cannabis will be assessed by 16 items of the “Knowledge about Cannabis” scale adapted from the SHAHRP questionnaire, as used in previous trials of the *Climate Schools* programs [18-21,23,24,37]. Students and parents would be required to answer “True” or “False” for each item, for example, *“Using cannabis can cause people to feel anxious, depressed (sad), paranoid (suspicious) and panicky,”* and a greater proportion of correct answers indicates greater cannabis knowledge.

###### Frequency of Alcohol Consumption

Students will be asked to report how frequently they consumed alcohol, in terms of standard drinks; this outcome will be measured by questions that were originally adapted from the SHAHRP “Patterns of Alcohol” index and have been used in previous *Climate Schools* trials [18-21,23,24,37,46]. Students would be asked questions such as*“How often did you have a standard alcoholic drink of any kind in the past 12 months?,”* with response options ranging from “Less than monthly” to “Daily or almost daily,” and higher scores indicating a higher frequency of alcohol consumption.

###### Frequency of Drinking to Excess

Students will be asked to report the frequency of drinking to excess (defined as having ≥5 standard drinks on a single occasion). These questions were originally adapted from the SHAHRP “Patterns of Alcohol” index and reflect those used in previous *Climate Schools* trials [18-21,23,24,37,46]. Students would be asked to report *“How often did you have 5 or more standard alcoholic drinks on one occasion in the past 12 months?”* with response options ranging from “Less than monthly” to “Daily or almost daily” and higher scores indicating a higher frequency of drinking to excess.

Additional measures include demographic information, such as gender, age, country of birth, truancy rates, and academic performance (to determine the baseline equivalence of groups), which will be assessed using questions that have been included in previous *Climate Schools* trials [18-21,23,24,37]. Students will also be asked to complete the Kessler 6 scale [47] to assess psychological distress in the past 30 days, and their quality of life will be measured by the Child Health Utility 9D scale [48]. Finally, students’ self-control will be measured using a 13-item scale developed by Tangney et al [49], which was used in the PAS program [32,33,42] and which includes questions such as *“I am good at resisting temptation*,*”* in which students would be asked to indicate how they typically are on a 5-point scale from “Not at all” to “Very Much.” These additional measures will be assessed at baseline and 12- and 24-month follow-up.

#### Assignment of Interventions

##### Allocation

Following school consent, schools have been randomly allocated to the CSP or control group by an external researcher; this process involved stratified random allocation, in which schools were divided into three mutually exclusive strata: (1) coeducational (mixed males and females) school, (2) single-sex or predominantly girls school, and (3) single-sex or predominantly boys school. The allocation was random within strata to achieve balance across intervention and control groups with respect to the number of males and females participating in the trial. Randomization was achieved using a randomization table created in StataSE, version 14, using the Stratarand procedure. The randomization sequence was computer-generated by an external biostatistician, who then informed the research team of which group each school had been allocated to.

##### Blinding (Masking)

It is not possible for the research team to remain blinded to the group allocation of schools during the study, given the nature of the intervention and the need to manage schools (particularly teachers as they progress through the program). However, the research team were not involved in the *allocation* of schools to the control or intervention groups, as this allocation was conducted externally, thereby removing the possibility of bias in the group allocation. Furthermore, the research team will not be in direct contact with the students or parents during the study (with the exception of students who are absent from school on the day of assessment; a list of absent students will be provided by the school teachers and these students will be contacted through email and invited to complete subsequent follow-up assessments by the research team). As such, no bias is likely to result from the research team’s knowledge of each school’s group allocation.

### Data Collection, Management, and Analysis

#### Data Collection

Students and parents will complete a self-assessment questionnaire online through the CSP website at baseline and 12- and 24-months postbaseline. The questionnaires contain scales used in previous *Climate Schools* trials, as well as specific parenting scales from the APSALS survey [44] and scales used to evaluate the effectiveness of the PAS program [42].

All measures are self-reported, as it has been found to be the most favored method of assessment for young people and has excellent discriminant [50] and predictive [51] validity [46,52]. Self-report has also previously been found to be a reliable method for assessing the frequency and quantity of adolescent alcohol use [53]. Furthermore, currently, no viable alternatives exist for data collection on alcohol use in an adolescent sample, as biological measures would not be appropriate in a sample at the early stages of alcohol use initiation [54].

##### Intervention Fidelity

Internet-based tracking will be used to monitor the extent to which students and parents engage with the intervention (ie, tracking the number of webinar views, the number of parents who ranked the rules, the number of parents who completed each module, the number of students who completed each lesson, etc). While teachers in the intervention group will be asked to complete a logbook as a record of how they delivered the intervention, teachers in the control group will complete a logbook detailing the type of drug and alcohol education they offered to their students over the same period.

##### Program Evaluation

Students, parents, and teachers in the CSP group will also be asked to complete two additional questionnaires, asking them to evaluate the intervention content that they received (ie, they will be asked how acceptable, appropriate, and enjoyable they found the program content). Teachers will be asked to indicate the likelihood that they would recommend the program to others, whereas students and parents will be asked to rate the likelihood that they would use the information and skills they learned in their own lives. Students and parents will be invited to complete these evaluation questionnaires once in 2018 after completing the *Alcohol* program and again in 2019 after completing the *Alcohol and Cannabis* program.

#### Retention

To facilitate the retention of students and parents in the trial, frequent communication will be maintained through email prompts generated from the CSP website, which reiterates the requirements of the study. Participants will also be offered reimbursement after completing each study questionnaire; specifically, students will be entered into a draw to win one of three Aus $500 JB Hi-Fi or Apple store vouchers at each assessment occasion, and parents will enter the draw to win one of three Aus $500 Westfield or Coles gift cards. Moreover, teachers will receive a one-off reimbursement of Aus $50 for the extra administration involved during the trial. When completing the baseline questionnaire at the beginning of the study, students and parents will be asked to enter their contact details (ie, name, address, home number, mobile number, and secondary email), which will be used solely for contacting students who are absent from school on the day of a questionnaire (absent students will be identified by their teacher, who will inform the research team of the absent students) and inviting them to complete subsequent follow-up assessments. Any data collected from students and parents who have consented but discontinue the study will be used in the analysis, in accordance with the intention-to-treat principle. The chosen statistical analysis techniques consider missing data resulting from participant discontinuation.

#### Statistical Analysis

In this study, primary and secondary outcomes will be analyzed in longitudinal analyses using multilevel mixed-effects regression models. The effects of highest interest are intervention × time interactions that reflect differences between intervention groups in the growth of each outcome over time. The multilevel modeling can account for the expected correlations between different observations of the same individual and between individuals in the same school [55], which would otherwise violate assumptions of independence in traditional regression models. Therefore, models used in these analyses will incorporate both random intercepts and slopes for time at the individual level and random intercepts at the school level. Mixed-effects regression approaches accommodate missing data through the maximum likelihood estimation, an approach that is superior to alternative missing data strategies such as pairwise deletion [56]. Maximum likelihood methods produce unbiased estimates when missing data are assumed to be either missing completely at random or missing at random [57].

Mixed-effects logistic regression with a logit link function will be applied when analyzing binary outcomes. A range of potential fixed effects and random effects structures will be compared using likelihood ratio tests and model fit statistics, such as the Akaike information criterion, to determine the best fitting model for each outcome. For all outcomes, between-condition effect sizes (eg, Cohen *d*) and odds ratios will be calculated along with their corresponding 95% CIs, to provide interpretable estimates of the intervention effects. All analyses will be conducted on an intention-to-treat basis, retaining and analyzing all students and parents in the groups they were originally allocated.

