The parent component for the CSP program is based on the successful Dutch Prevention of Alcohol Use in Students (PAS) program [31-33] and was adapted for Australia in consultation with Australian parents and education and health experts [16]. The parent component of the CSP program is designed to be delivered entirely online, across the same school terms as the student *Climate Schools* program. The parent component targets modifiable parenting factors associated with adolescents’ alcohol and cannabis initiation and misuse [10,34], including rule-setting, parental supply, modeling, and monitoring. The parent component comprises introductory webinars, a rule-ranking component, internet-based modules, and internet-based parent summaries of the material covered in the student program. A complete description of the parent component can be found in a development paper published by the members of the research team [16].

Currently, we are seeking to evaluate the effectiveness of the CSP program in preventing alcohol and cannabis use and increasing parents’ self-efficacy to prevent their child from using these substances. Incorporating an internet-based parent component into an effective school-based student program has the potential to remarkably enhance prevention outcomes and reduce alcohol- and cannabis-related harms among adolescents.

We will determine the effectiveness of the CSP intervention by running a cluster RCT in Australian Independent and Catholic secondary schools (ACTRN12618000153213). Cluster randomization will be used to avoid contamination of the control group with the intervention groups through student and staff communication. Schools will be randomly allocated to the CSP condition or the “control” condition. Students and parents in the CSP condition will be provided access to the *Climate Schools*: *Student* component and the *Climate Schools Parenting Program*, respectively, whereas students in the control condition will receive their health education classes as usual, which covers alcohol and other drug education topics. Students and parents in both groups will complete self-report surveys at baseline and 12 and 24 months postbaseline. Figure 1 depicts the study design.

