##### Sample Size

For cluster randomization, sample size calculations were based on sample size requirements developed by Heo and Leon [35] to detect the intervention by time interactions in longitudinal cluster randomized clinical trials. This trial is powered to detect differences in the overall student sample across three time-points. Five schools, with an average of 70 students per school, are required per intervention group; this would achieve an 80% power to detect a standardized, between-group mean difference of 0.2 (*P*=.05) in primary outcomes at the end of the trial, with 3 measurement occasions. An effect size of 0.2 is comparable with previous trials of combined student and parent programs (effect size range: 0.2-0.3) [36]. To account for school dropouts during the trial, which we expect to be approximately 15%, we aim to recruit at least 12 schools in total. Assuming that the majority (if not all) students in the year group participate in this study (approximately 70 on average; based on participation rates found in previous school-based trials of a similar nature [18-21,23,24,37]), it will give us a total of 700 students from 10 schools at the baseline to test the effect of the intervention.

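### The stated model has no school-level random effect for change over time, so the intervention × time test can be anti-conservative, by an amount the protocol does not let one fix

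*Protocol article*

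**What the plan says.** All of this is in the protocol article; no statistical analysis plan was available.

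- **Unit of randomisation** (Introduction): "Schools will be randomly allocated to the CSP condition or the “control” condition".
- **Main test** (Statistical Analysis): "The effects of highest interest are intervention × time interactions that reflect differences between intervention groups in the growth of each outcome over time".
- **Random effects** (same section): "random intercepts and slopes for time at the individual level and random intercepts at the school level".
- **Possible departure from that structure** (same section): "A range of potential fixed effects and random effects structures will be compared using likelihood ratio tests and model fit statistics". The aim is the best-fitting model for each outcome. A school-level time effect is neither named nor excluded, and no small-sample method is named.
- **Size** (Sample Size): "Five schools, with an average of 70 students per school, are required per intervention group", to "achieve an 80% power to detect a standardized, between-group mean difference of 0.2" at the 5% level with three measurement occasions. At least 12 schools are to be recruited, to allow for about 15% school dropout. The section gives no intraclass correlation, no within-student correlation and no between-school variance of change.
- **Outcome type** (Primary Outcomes): both primary outcomes are yes/no and go to mixed-effects logistic regression.

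**The concern.** In a cluster-randomised trial the standard error of the treatment effect has to contain the between-cluster variation of whatever is being contrasted. Here that is change over time. A school random intercept shifts a school's level equally at every occasion, so it cancels from a difference in growth. The only random term left that varies with time is the student's own slope. The interaction is therefore tested as if students' changes were independent within a school.

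The article gives reasons to expect school-specific trends. Control schools teach their own drug and alcohol education, and logbooks are kept to record what was taught. The classroom activities in the programme are optional and teacher-led. Parents' rules are ranked and shared school by school. Schools also differ in sex composition. Nothing in the article supports a between-school variance in growth of exactly zero.

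At stake is the nominal 5% level of the main test, and the width of the interval for the interaction, for both primary outcomes.

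**Working it through.** **Inputs from the protocol article.** 5 schools per arm (10 analysed, 12 recruited), m = 70 students per school (350 per arm), standardised difference 0.2 at the end of the trial, 80% power, α = 0.05 (taken as two-sided), 3 occasions.

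**Assumed.** ρ, the share of the variance in student change that lies between schools. It is not in the article, so a range is shown.

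**1. The plan's own figure.** For three equally spaced occasions, outcome SD 1, within-student correlation r and no school × time variance, the variance of the difference in slope is 2·[(1−r)/2]/350 = (1−r)/350. The slope difference is 0.2/2 = 0.1 per year.

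- With r = 0.554: SE = √(0.446/350) = 0.0357, z = 0.1/0.0357 = 2.80, power 80%.
- With r = 0.5 the power is 75%; with r = 0.6 it is 84%.

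The stated 80% is attainable if r is about 0.55 and schools do not differ in trend. It cannot be reproduced from the stated inputs alone. The dropout allowance agrees: 10/0.85 = 11.8, so 12 schools.

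**2. Type I error with a school intercept only.** In a balanced linear model the true variance of the interaction is DE = 1 + (m−1)ρ = 1 + 69ρ times the variance the model uses. The actual error is 2Φ(−1.96/√DE).

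| ρ | DE | Type I error | Ratio to 5% |
|---|---|---|---|
| 0 | 1.00 | 5.0% | 1.0 |
| 0.002 | 1.14 | 6.6% | 1.3 |
| 0.005 | 1.34 | 9.1% | 1.8 |
| 0.01 | 1.69 | 13.2% | 2.6 |
| 0.02 | 2.38 | 20.4% | 4.1 |
| 0.03 | 3.07 | 26.3% | 5.3 |

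A simulation (20,000 balanced, complete trials per setting, continuous outcome, 10 and 12 schools) agreed, for example 12.9-13.2% at ρ=0.01 and 20.4-21.0% at ρ=0.02.

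**3. With the school slope chosen by fit.** The same simulation applied AIC and two likelihood ratio cut-offs. Ranges span these rules, z or t inference once the slope is selected, and 10 or 12 schools.

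| ρ | Slope selected | Type I error after selection |
|---|---|---|
| 0.005 | 4-13% | 8-9% |
| 0.01 | 13-28% | 9-12% |
| 0.02 | 35-59% | 10-15% |
| 0.03 | 55-78% | 8-15% |

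The error is lower than in step 2, most clearly at larger ρ, but about 1.5- to 3-fold inflation remains.

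**4. Binary outcome, rough check.** This used 1,000 trials per setting, 12 schools, assumed prevalences of 8%, 18% and 34% at the three occasions, and a logistic model with fixed school intercepts and student-clustered standard errors standing in for the planned model. Type I error was 4.6%, 6.5%, 7.3%, 9.1% and 14.4% for school-slope SDs of 0, 0.1, 0.15, 0.2 and 0.3 logit per year. With 1,000 trials the simulation error near 6.5% is √(0.065·0.935/1000) ≈ 0.8 percentage points, so the smaller values are imprecise.

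**5. After correction.** A t test at school level, equivalent in the balanced case to a school random slope with schools−2 degrees of freedom, held 4.8-5.2% throughout. The degrees of freedom matter: a school-level variance estimate referred to 1.96 gives about 8.6% with 10 schools (8 df) and 7.8% with 12 (10 df), even with the slope included.

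For power, suppose the stated 80% assumes no school × time variance. The noncentrality is (1.96+0.84)/√DE with 10 schools, multiplied by √(12/10) with 12, on schools−2 df.

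| ρ | 10 schools | 12 schools |
|---|---|---|
| 0 | 69% | 79% |
| 0.005 | 56% | 67% |
| 0.01 | 47% | 57% |
| 0.02 | 36% | 44% |

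**The case against.** **Detail is left to the analysis plan, and a school slope could still be added.** The article does not merely stay silent: it states which random effects the models will contain and which contrast matters most. The fit-based comparison is a real mitigation, and the error rates in step 2 are not those of the full planned procedure. But it guarantees nothing, and step 3 shows what remains. With so few schools, fit statistics are a weak basis for deciding whether the unit of randomisation is respected.

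**A reader might infer that about 700 students are treated as independent.** That goes too far. Correlation within a school in the level of the outcome is modelled. Only changes over time are treated as independent within schools.

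**The calculations use continuous, balanced, complete data, while the primary outcomes are binary.** This stands. Exact cancellation of the school intercept is a linear-model result and only approximate on the logit scale. The binary check supports the direction, but nothing binary supports errors of 20% or more.

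**The Planned Comparisons section also compares the arms at each occasion, and 24 months is the primary endpoint.** In a contrast at a single occasion the school intercept does enter the standard error. Over-narrow intervals are therefore shown for the interaction, not for every planned contrast. These comparisons do not replace the interaction as the main test.

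**Conclusion.** The point holds, conditionally. Under the stated structure the main test omits between-school variation in change, and it is anti-conservative whenever schools differ in trend for reasons other than the programme.

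The size rests on an assumed ρ. Without a school slope, and for a continuous outcome with 70 students per school, it runs from no inflation at ρ=0 to about 9%, 13% and 20% at ρ=0.005, 0.01 and 0.02. With selection by fit, about 1.5- to 3-fold inflation remains for ρ of 0.005-0.03. For the binary primary outcomes the rough check gives about 6.5-14% for school-slope SDs of 0.1-0.3 logit per year.

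A reader might conclude that type I error is inflated two- to four-fold. The article does not support that as a fact: without a school slope it requires ρ between about 0.006 and 0.019, and the article gives no value.

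**What to change.** 1. Prespecify a school × time random effect in the model for each primary outcome: a school random slope, or school-by-occasion effects if time is categorical. Keep it whatever its estimated size and whatever the likelihood ratio tests or AIC suggest.
2. Name a small-sample method based on the number of schools, for example schools−2 degrees of freedom. Adding the random effect but testing against 1.96 would still leave about 8-9%.
3. Alternatively, make a school-level analysis of the 24-month outcome the primary analysis.
4. Restate the power in the Sample Size section with an explicit between-school variance of change and the within-student correlation used.

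The text change is short, but the cost is real. Intervals become wider and the stated power falls. If the 80% assumes no school × time variance, it becomes about 69% at ρ=0 and 47% at ρ=0.01 with 10 schools, or 79% and 57% with 12.

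### With 10 to 12 schools, large-sample maximum likelihood tests are anti-conservative for contrasts that carry school-level variance, so between-school degrees of freedom should be specified

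*Protocol article*

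**What the plan says.** All of this is in the protocol article.

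- **Number of schools (Sample Size).** "Five schools, with an average of 70 students per school, are required per intervention group", and after allowing for loss of schools "we aim to recruit at least 12 schools in total".
- **Effect of interest (Statistical Analysis).** "The effects of highest interest are intervention × time interactions that reflect differences between intervention groups in the growth of each outcome over time".
- **Random effects (Statistical Analysis).** The models have "random intercepts and slopes for time at the individual level and random intercepts at the school level". No school-level time effect is written down, although alternative fixed and random structures are to be compared by likelihood ratio tests and the Akaike criterion.
- **Estimation (Statistical Analysis).** "Mixed-effects regression approaches accommodate missing data through the maximum likelihood estimation". Binary outcomes, which include both primaries, get mixed-effects logistic regression. Effect estimates carry 95% confidence intervals.
- **Group comparisons (Planned Comparisons).** The intervention and control groups are compared on each outcome at baseline, 12 and 24 months. The Outcomes section makes 24 months the primary endpoint.

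The article does not give the reference distribution for the intervention test, a degrees-of-freedom method or an ICC.

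**The concern.** Schools are the randomised units. When a contrast between groups contains school-level variance, that variance is estimated from 10 or 12 schools, which leaves 8 or 10 degrees of freedom. Large-sample inference then errs in two ways. Maximum likelihood divides the between-school sum of squares by the number of schools rather than by schools minus 2, and 1.96 is used where a t value of 2.31 or 2.23 is needed. Both make standard errors or critical values too small. A benefit of the program at 24 months could be declared at a true error rate well above 5%, with confidence intervals that under-cover to match. Mixed logistic software ordinarily reports large-sample Wald or likelihood ratio results, so an analyst who follows the text as written would probably use them.

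**Working it through.** **Inputs from the article.** 5 schools per group, 70 students per school, standardised difference 0.2, 80% power, P=.05 (taken as two-sided), 3 occasions, about 15% school dropout, at least 12 schools.

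**Assumptions (not in the article).** School ICC of the tested contrast 0 to 0.10. Within-student correlation 0.5 to 0.6. Logistic simulation: school intercept SD 0.4, school slope SD 0 or 0.25, student intercept SD 1.5, no student slope.

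**1. The plan's own size.** The calculation is said "to detect the intervention by time interactions in longitudinal cluster randomized clinical trials". With times 0, 1, 2, the sum of squared deviations is 2 and the slope difference is 0.2/2 = 0.1, so n per group = 2(1−ρ)(1.96+0.8416)²/(2 × 0.1²).
- ρ = 0.50: 392 students, 5.6 schools; 350 students give 75% power.
- ρ = 0.55: 353 students, 5.0 schools; 80% power.
- ρ = 0.60: 314 students, 4.5 schools; 84% power.

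The stated size is therefore reached at an unstated ρ of about 0.55, with normal critical values and no school-level variance in the slope. For dropout, 10/(1−0.15) = 11.8, so 12 schools is reproduced.

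**2. Upper limit of the inflation.** Balanced linear model, school variance dominating, J schools:
- ML Wald: P(|t on J−2 df| > 1.96√((J−2)/J)). The cut-off is 1.753 for J = 10 and 1.789 for J = 12, giving **11.8%** and **10.4%**.
- Likelihood ratio: P(|t| > √((J−2)(exp(3.84/J)−1))). The cut-off is 1.936 and 1.942, giving **8.9%** and **8.1%**.
- REML with z: P(|t| > 1.96), giving **8.6%** and **7.8%**.

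**3. Finite ICC.** Correctly specified linear model, 70 per school, 200,000 null trials per setting. Rejection rate at nominal 5%, 10 schools / 12 schools:

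| ICC of contrast | ML Wald z | Likelihood ratio | REML z | School-level t, J−2 df |
|---|---|---|---|---|
| 0 | 0.045 / 0.045 | 0.039 / 0.040 | 0.039 / 0.039 | 0.050 / 0.050 |
| 0.005 | 0.071 / 0.068 | 0.058 / 0.057 | 0.058 / 0.056 | 0.050 / 0.050 |
| 0.01 | 0.087 / 0.083 | 0.070 / 0.068 | 0.069 / 0.067 | 0.050 / 0.050 |
| 0.02 | 0.106 / 0.097 | 0.082 / 0.077 | 0.080 / 0.075 | 0.050 / 0.050 |
| 0.05 | 0.116 / 0.103 | 0.088 / 0.081 | 0.085 / 0.078 | 0.050 / 0.051 |
| 0.10 | 0.116 / 0.103 | 0.088 / 0.080 | 0.085 / 0.078 | 0.049 / 0.050 |

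**4. Binary outcome, intervention × time.** Three occasions, 1,000 null trials per setting; Monte Carlo standard error about 0.007 at 0.05. Results for 10 / 12 schools:
- School intercept only, both in truth and in the model: Wald and likelihood ratio both 0.049 / 0.041. No inflation, because the school intercept cancels from the interaction.
- School slope present (SD 0.25) and fitted: Wald 0.084 / 0.077, likelihood ratio 0.065 / 0.064. The likelihood ratio figures lie only about two Monte Carlo standard errors above 0.05.
- School slope present but left out of the model: about 0.14 for either test and either number of schools.

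**5. Cost of using t.** t(.975) is 2.306 on 8 df and 2.228 on 10 df.
- Against z: 2.306/1.96 = 1.18 and 2.228/1.96 = 1.14.
- Against ML Wald intervals when school variance dominates, multiply by √(10/8) or √(12/10): 1.32 and 1.25.
- Power at the noncentrality (2.80) that gives 80% with z: 69% on 8 df, 71% on 10 df.

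**The case against.** The strongest reply is that the article never commits the error. The sentence on maximum likelihood is about missing data, likelihood ratio tests are named only for choosing a model, and no z or chi-square reference is given for the intervention test. A degrees-of-freedom method is the kind of detail that a protocol article may leave to the analysis plan. This stands as a limit: the point is conditional on the usual large-sample inference being used. It does not remove the point, because the article fixes the estimator and the number of schools, and nothing in it departs from the default.

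The second reply is also right in its scope. A reader might infer that every maximum likelihood test in this trial is anti-conservative even if the model is correct, and that the false-positive rate of both primary outcomes exceeds 5% regardless. The documents do not support that. If the school-intercept-only model is exactly true, intervention × time rests on about 700 students and the tests are at their nominal level (step 4).

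Third, the 8% to 12% figures come from a linear model with dominant school variance, while the primaries are binary. The logistic figures are smaller, and at an ICC of 0.005 the likelihood ratio test is barely affected.

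Fourth, the omitted school-by-time effect is the larger threat to intervention × time (0.14 in step 4), and a degrees-of-freedom correction alone does not repair that. Equally, adding the slope alone leaves the Wald test at about 8%.

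**Conclusion.** The point holds for contrasts that carry school-level variance, provided large-sample inference is used. These contrasts are the group comparisons at 12 and 24 months, which include the primary endpoint and contain the school intercept even in the model as written, and intervention × time once a school-level time effect is in the model. Nominal 5% becomes about 6% to 12% in a correctly specified linear model at ICC 0.005 to 0.10, and about 6.5% to 8.5% in the logistic model with a fitted school slope.

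The direction is stable; the size depends on ICC and variance values that the article does not give. The single-occasion comparison was worked for the linear model only, so its size for the binary primaries is inferred by analogy. This merits a specified method, but it does not show that the planned intervention × time test is invalid as written.

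**What to change.** State in the analysis plan:

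1. A school-by-time random effect in the models for intervention × time, in addition to the school intercept.
2. Inference on between-school degrees of freedom. For continuous outcomes, use REML with Kenward-Roger or Satterthwaite. For the binary primaries, use t with schools minus 2 degrees of freedom, less stratum terms, or GEE with a small-sample-corrected sandwich variance.
3. A permutation check of each primary outcome within the allocation strata, where the number of possible allocations permits. Equal groups without strata would allow at most 252 allocations for 10 schools and 924 for 12. The three strata reduce this, and their sizes are not reported.
4. An acknowledgement in Sample Size that "80% power to detect a standardized, between-group mean difference of 0.2" becomes about 69% to 71% with these degrees of freedom, before any added school-level variance in the slope.

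The cost is wording, software options and precision. Intervals are about 14% (12 schools) to 18% (10 schools) wider from the t value alone, and about 25% to 32% wider than ML Wald intervals when school variance dominates. Two stratum terms would leave 6 or 8 degrees of freedom (10−2−2, 12−2−2) and widen them further. REML with a fixed t reference is conservative when school variance is near zero: 0.016 (10 schools) and 0.020 (12 schools) at ICC 0 in the linear simulation. A school-level t test stays at 0.05 there.
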